#### *High-density EGG assessment of stomach activity*

We will use the Alimetry device to perform high density mapping of gastric motility. Briefly, this entails a 64 channel EGG assessment of gastric motility (Gharibans et al., 2017, Gharibans et al., 2018) following consumption of a small meal. Participants will arrive on an empty stomach and will then consume a liquid milkshake meal (containing approximately 600 kCal). For the next three hours they will lay recumbent on a couch will periodically providing ratings of gastric sensation including feelings of fullness/bloating, hunger, and satiety. During this period, participants will also enter sensation and emotion ratings via the Somatomap application. A major advantage of this device is the ability to obtain measurements of gastric movement without resorting to imaging methods such as fluoroscopy, which involve exposure to much higher amounts of radiation than abdominal X-rays (e.g. 6 mSV which is the equivalent of 2 years of natural background radiation).

#### *Follow up:*

Follow up will be collected remotely at three time points (1month, 3 months, 6 months) by having the participants complete rating scales in Redcap while in their home environment. Participants will be requested to complete these scales within 14 days of receiving them; however, responses uploaded outside of this time frame will also be accepted.

#### *Physiological measurement during testing:*

Heart rate (ECG), respiration, skin conductance, pulse oximetry, electroencephalography (EEG), and electrogastrogram will be recorded continuously using BIOPAC instrumentation (Goleta, California) or EEG (Brain Products GmbH, Germany) during each stimulation session. EEG is a non-invasive measure of brain function that is compatible with the Vibrant Capsule. During the second capsule stimulation visit continuous ECG, EEG, and EGG will not be recorded; however, we will record vital signs before and after stimulation as noted in the next section.

#### *Safety monitoring during testing*

Physiological vital signs will be recorded during the screening enrollment visit by a trained member of the study team present in the room. Following this initial visit, these

vital signs will be closely monitored by nursing staff and physicians on the inpatient unit. The study team will have full access to all vital sign data. Participants will be closely monitored for signs of discomfort or increased anxiety. Individuals reporting increased anxiety levels at any time during the assessment will be offered the opportunity to discontinue the study. Any participant displaying abnormally high elevations in pulse range (e.g. HR >120 bpm) or blood pressure (e.g. Systolic BP > 160, or Diastolic BP >100) will be excused from the study. During stimulations participants will be monitored by a trained member of the study team. A clinically trained member of the team (RN or MD) will always be available in the building during the stimulations in case additional participant monitoring is needed. In the event of emergency, the first responder alerting procedures will be followed, as specified in the emergency protocol section (below).

#### **E. Statistical Methods:**

Data will be analyzed using standard univariate and multivariate statistical parametric methods except for instances that require the use of non-parametric statistical analysis. Examples of these methods include linear mixed-effects models with Group (or stimulation condition) as the fixed-effect, and (a) random intercept only (equivalent to exchangeable correlation structure) or (b) random time/stimulation slope to capture temporal correlation at the 0.05 significance level (i.e., group by time effects). Additional statistical measures such as ANCOVAs, t-tests, and correlation analyses may be undertaken. There are no previous studies that have used this stimulation protocol (as it has not yet been developed), to assist in estimating expected effect sizes. Since there have been no prior analogous mechanosensory assays of stomach interoception in AN, we based our target sample size on the estimated proportional difference in relapse rates without treatment over the 6 month period following discharge (Aim 2a), taking into account estimated relapse rates for AN from the literature and possible expression of eating psychopathology in HC. Our prior literature review ([name] et al, 2017, J Eat Dis) suggested lifetime relapse rates between 30-50%, with the highest risk occurring within the first year after inpatient discharge. **Taking a conservative approach (equivalent to a medium effect size), we estimated a relapse probability of 25% within the AN sample** and an expression rate of 5% within the HC sample over the course of the study period. Detecting differences between these two independent proportions (95% power (1-beta error probability) at an alpha error probability of 0.05, G\*Power 3.1231) yielded a total sample size of 130 subjects (n=65 completers per group; note that we aim to recruit 115 participants per group to account for an estimated 20% dropout rate across all study phases). During data processing, analysts will remain blinded to group membership whenever possible.

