**Aim 2: To determine the clinical relevance of expectation-based interoceptive dysregulation in AN**

Hypothesis 2a: Computational and neurophysiological individual difference measures collected during the stimulation of stomach sensations with a vibrating capsule (pGI, IP,  $\eta$ , event related potential, ERP amplitude) will accurately predict post-discharge outcomes (relapse or remission) in AN at 1, 3, and 6 months. Lower IP and  $\eta$ , stronger influences of pGI, and lower ERP amplitude will be predictive of poorer outcomes.

Hypothesis 2b: Computational and neurophysiological measures will be associated with measures of AN illness severity (lowest BMI, current eating disorder severity).

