Preliminary studies: The Vibrant capsule was developed by Vibrant Ltd, with the intention of providing a non-pharmacologic therapeutic option for chronic constipation. It consists of an orally administered non-biodegradable vibrating capsule, that is wirelessly activated using an activation base unit. An initial clinical trial study examined the safety of this approach first in canines, and secondarily in healthy human volunteers (Ron et al., 2015) (clinicaltrials.gov: NCT01306448). After no adverse events were noted in these participants, as part of the same trial an open label safety study was conducted in 26 patient with chronic constipation, who received the Vibrant capsule twice a week for 7.5 weeks. There were no serious adverse events, all capsules were expelled without difficulty, and any minor adverse events (e.g. abdominal pain, diarrhea, flatulence) were transient. Subsequent to this study, a larger prospective randomized multi-center placebo controlled clinical trial testing the efficacy of the Vibrant capsule for treatment of chronic idiopathic constipation has been initiated (see WIRB® Protocol #20190204). The Vibrant capsule has been designated by the US Food and Drug Administration as a 501K De-Novo regulatory path (i.e., non-significant risk device).

During the previous WIRB protocol (WIRB # 20190971), we adapted the Vibrant

capsule to deliver mechanosensory stimulation to the stomach, and we have demonstrated the safety of this procedure in 40 healthy (21 male, 19 female) and 5 AN females, all with BMIs above 18.5 and ages within 13 to 40 years (our current proposed criteria is between ages 15 to 40 years). There were no adverse events or severe adverse events in any group. We observed no evidence of nausea, dizziness, or pain (0 out of 40 HC, 0 out of 13 AN). We have seen no evidence of increased anxiety on the State-Trait Anxiety Inventory (STAI) in HCs (pre STAI mean 27, post STAI mean 28) or ANs (pre STAI mean 46, mean post STAI 44). Further, across several inpatient focus groups the majority (>70%) of AN patients (n=25) expressed more favorable attitudes toward an ingestible capsule approach versus other cardiac, respiratory, or invasive GI methods.

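### The sample-size calculation labelled Aim 2a compares relapse in AN with expression in HC, so its 95% power does not apply to Hypothesis 2a, which is prediction within AN

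*Protocol*

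**What the plan says.** The protocol's Section E (Statistical Methods) ties the target size to a named aim, the "estimated proportional difference in relapse rates without treatment over the 6 month period following discharge (Aim 2a"). Two inputs follow. For AN, "we estimated a relapse probability of 25% within the AN sample". The figure for healthy comparisons is "an expression rate of 5% within the HC sample over the course of the study period". The test is described as "Detecting differences between these two independent proportions (95% power (1-beta error probability) at an alpha error probability of 0.05", and it "yielded a total sample size of 130 subjects (n=65 completers per group". Recruitment is set at 115 per group, with a 20% dropout rate given as the reason.

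Hypothesis 2a, under Aim 2, is worded differently. The prior-expectation parameter, interoceptive precision, learning rate and ERP amplitude "will accurately predict post-discharge outcomes (relapse or remission) in AN at 1, 3, and 6 months".

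The other hypotheses are 1a and 1b (AN against HC on perceptual, EEG and EGG measures) and 2b (association of the measures with AN severity).

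Section E explains the choice of basis by the lack of earlier data: "There are no previous studies that have used this stimulation protocol (as it has not yet been developed"). Section C reports of the earlier project that "we have demonstrated the safety of this procedure in 40 healthy (21 male, 19 female) and 5 AN females", and Section B says that project developed the probe in healthy individuals and inpatients with AN.

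**The concern.** The calculation and the aim it is assigned to are different questions. The calculation asks whether AN patients relapse more often than healthy women show eating psychopathology. Hypothesis 2a asks whether, among AN patients, those who relapse had different baseline measures from those who do not. HC participants carry no information on that second question, and its information depends on the number of relapses in the AN group alone.

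At stake is how the Aim 2a result will be read. With the label as printed, a null finding could be taken as well-powered evidence that these markers do not predict relapse. A positive finding could be taken as precise enough to support the word accurately in the hypothesis. The protocol gives no figure that supports either reading. It also gives no size statement for the AN-HC contrast in Aim 1, which is the comparison the two-group design does serve.

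**Working it through.** **1. The plan's own figure.** Inputs from Section E: p1 = 0.25, p2 = 0.05, alpha 0.05 (sidedness not stated), power 0.95, equal groups.

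Unpooled formula: n per group = (z_alpha + z_beta)² × [p1(1−p1) + p2(1−p2)] / (p1−p2)².

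Variance term: 0.1875 + 0.0475 = 0.235. Squared difference: 0.04.

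- One-sided: (1.645 + 1.645)² × 0.235 / 0.04 = 63.6, so 64 per group, 128 in total. Pooled power at 65 per group is 94.7%.
- Two-sided: (1.960 + 1.645)² × 0.235 / 0.04 = 76.3, so 77 per group, 154 in total. Pooled power at 65 per group is 90.1%.

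The printed 130 is therefore reproduced, to within 2, as a one-sided comparison of AN with HC. It is a valid kind of calculation for that comparison.

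**2. Which hypothesis uses it.**

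| Hypothesis | Comparison | Uses AN relapse vs HC expression? |
|---|---|---|
| 1a | AN vs HC, perceptual parameters | No |
| 1b | AN vs HC, EEG and EGG responses | No |
| 2a | Prediction of relapse or remission within AN | No |
| 2b | Association with severity of AN | No |

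**3. What the AN sample gives for Hypothesis 2a.** Two completer counts are carried because the protocol's figures support both: the stated 65, and 115 × 0.80 = 92. Relapse is 25%, as in Section E.

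- 65 completers: 0.25 × 65 = 16.25 relapses, 48.75 without.
- 92 completers: 23 relapses, 69 without.

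Standard error of a standardised mean difference between relapsers and non-relapsers: SE = √(1/(0.25n) + 1/(0.75n)).

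- n = 65: SE = 0.286
- n = 92: SE = 0.241

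Difference detectable with 80% power, two-sided 0.05, one predictor, no multiplicity: (1.960 + 0.842) × SE.

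- n = 65: 0.80 SD
- n = 92: 0.67 SD

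For 95% power: (1.960 + 1.645) × SE = 1.03 SD and 0.87 SD.

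**4. Power under assumed effects.** The protocol gives no predictor effect size, so these are illustrations. The normal approximation is Φ(d/SE − 1.960); noncentral t results are alongside.

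| Assumed d | n = 65, normal / t | n = 92, normal / t |
|---|---|---|
| 0.5 | 41.5% / 40.5% | 54.6% / 53.8% |
| 0.8 | 79.8% / 78.5% | 91.4% / 90.8% |

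Sensitivity at d = 0.5, from 65 to 92 completers: one-sided 54–67%; Bonferroni over four predictors 21–32%; 50% relapse 51–66%. With all 115 retained and 25% relapse, power is 63–64%.

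**5. Precision of an AUC.** Hanley–McNeil with A = 0.70: Q1 = A/(2−A) = 0.538 and Q2 = 2A²/(1+A) = 0.576. Variance = [A(1−A) + (m−1)(Q1−A²) + (k−1)(Q2−A²)]/(mk), with m relapsers and k non-relapsers.

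- n = 65: SE = 0.080, 95% interval ±1.96 × 0.080 = ±0.16
- n = 92: SE = 0.067, 95% interval ±1.96 × 0.067 = ±0.13

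**6. Aim 1.** Two-sample t test, two-sided 0.05, 80% power: detectable d = 0.495 at 65 per group and 0.415 at 92 per group.

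**The case against.** The best defence is that Section E is open about its basis. It says there were no analogous assays in AN, turns to relapse rates instead, and attaches the 95% to the two proportions. It nowhere prints 95% power for prediction within AN. That is true, but the aim label in the same passage invites exactly that reading, and nothing corrects it.

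A second objection is that Hypothesis 2a has outcomes at three times and that the purpose section speaks only of regression-based approaches. The simple comparison of relapsers with non-relapsers used here is therefore not the protocol's model. This stands as a limit on the figures. A different model would change them, but it would not bring HC participants into a within-AN question.

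Three stronger readings are tempting and are not supported:

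- A reader might infer that Aim 2a simply has 41–55% power. The 0.5 SD behind that range is an assumption. The protocol's reference to a medium effect describes 25% against 5%, not a predictor difference.
- A reader might infer that four predictors on 16 to 23 relapses are bound to overfit. That presumes a single unpenalised model with all four, which the protocol does not fix. The choice of model may properly sit in the SAP.
- A reader might infer that the pilot supplied effect sizes or SDs that were ignored. Section C reports safety, symptom counts and mean anxiety scores. It gives no SDs and nothing on the parameters in Hypothesis 1a or on ERP amplitude.

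It is also fair to say that no inadequacy is shown for Aim 1: a detectable d of about 0.4 to 0.5 is reasonable, but unstated.

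**Conclusion.** The point holds. The label is wrong on the face of the document, and that part needs no assumption: the calculation is AN against HC, Hypothesis 2a is within AN, and no hypothesis tests what was calculated.

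The size of the gap is conditional. It rests on the plan's 25% relapse rate, 65 to 92 AN completers, one predictor, a two-sided 0.05 test and no multiplicity. Under those conditions only differences of about 0.67 to 0.80 SD are detectable with 80% power. At either assumed effect, 0.5 or 0.8 SD, power is below 95%; reaching 95% would take a true difference of about 0.87 to 1.03 SD.

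This does not show that the trial must be enlarged, or that Aim 2a will fail. It shows that the protocol claims a strength for a named aim that its calculation does not provide.

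The remark that the stimulation protocol is undeveloped also conflicts with Sections B and C. That is an inconsistency of wording and does not by itself prove that usable planning values existed.

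**What to change.** In Section E:

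1. Remove the Aim 2a label from the two-proportion calculation, and say that its 95% power does not apply to the prediction aim.
2. For Aim 2a, state the AN-only figures: about 16 to 23 expected relapses, a detectable difference of about 0.80 to 0.67 SD with 80% power, and an interval of about ±0.16 to ±0.13 around an AUC of 0.70, with the assumptions. Say that a null result will be interpreted against these figures.
3. For Aim 1, state the standardised detectable difference: about d = 0.50 at 65 per group or 0.42 at 92 per group, with 80% power.
4. Reconcile the statement that the stimulation protocol has not been developed with the pilot work in Sections B and C.

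The cost is protocol wording and a short calculation. Enrolment does not change. The drawback is that the stated power for Aim 2a becomes less favourable.

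### The 95% power claimed for 65 completers per group holds only for an undeclared one-sided test; at two-sided 0.05 it is about 90%

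*Protocol*

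**What the plan says.** The only sample-size justification is in Protocol section E, Statistical Methods. It rests on two assumed proportions. For the AN group the text reads "we estimated a relapse probability of 25% within the AN sample". For the healthy comparisons it takes "an expression rate of 5% within the HC sample over the course of the study period". The aim of the calculation is put as "Detecting differences between these two independent proportions (95% power (1-beta error probability) at an alpha error probability of 0.05". The software named is G*Power, and the result is that it "yielded a total sample size of 130 subjects (n=65 completers per group". The same sentence sets recruitment at 115 per group, citing 20% expected dropout.

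Neither the test nor its sidedness is given. The only other mention of a significance level in the section concerns the mixed-effects models, "to capture temporal correlation at the 0.05 significance level", and it too names no side.

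**The concern.** Sidedness is the one missing input that decides whether the calculation's answer is right. A reader who sees alpha 0.05 for a difference between two proportions, with no direction stated, will normally take it as two-sided. On that reading, 65 per group should give 95% power for 25% against 5%, and it does not.

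At stake is the figure that the protocol attaches to 65 completers. If the study finished with exactly that number, it would be reported as meeting a 95% power target. On a two-sided test the type II error would then be about 10%, not 5%.

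**Working it through.** **Inputs, all from Protocol section E.** p1 = 0.25 (AN), p2 = 0.05 (HC), difference d = 0.20, alpha 0.05, power 95%, equal groups, stated n = 65 per group. Sidedness is not stated, so both cases are run.

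Mean proportion = (0.25 + 0.05)/2 = 0.15. Pooled variance term = 2 × 0.15 × 0.85 = 0.255, square root 0.5050. Unpooled variance term = 0.25 × 0.75 + 0.05 × 0.95 = 0.235, square root 0.4848.

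**Step 1. Reproduce the protocol's figure (pooled normal approximation).**

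n = [z(alpha) × 0.5050 + z(power) × 0.4848]² / d²

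- One-sided: (1.645 × 0.5050 + 1.645 × 0.4848)² / 0.04 = 1.628² / 0.04 = 66.3, so 67 per group.
- Two-sided: (1.960 × 0.5050 + 1.645 × 0.4848)² / 0.04 = 1.787² / 0.04 = 79.8, so 80 per group.

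The stated 65 is within two participants of the one-sided answer and 15 below the two-sided one.

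**Step 2. Power at 65 per group (same formula).**

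power = Φ{[d√n − z(alpha) × 0.5050] / 0.4848}, with 0.20 × √65 = 1.6125

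- One-sided: Φ[(1.6125 − 0.8306)/0.4848] = Φ(1.613) = 94.7%.
- Two-sided: Φ[(1.6125 − 0.9897)/0.4848] = Φ(1.285) = 90.1%.

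**Step 3. Does the choice of method explain the gap?** The protocol does not name the test, so the usual alternatives were tried.

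| Method | One-sided: power at 65 | Two-sided: power at 65 | Two-sided: n per group for 95% |
|---|---|---|---|
| Pooled z formula | 94.7% | 90.1% | 80 |
| Unpooled z formula | 95.4% | 91.4% | 77 |
| Arcsine formula | 96.0% | 92.5% | 74 |
| Pooled z, full enumeration | 96.2% | 92.1% | 74 |
| Unpooled z or likelihood ratio, full enumeration | 96.2% | 92.8% | 74 |
| Fisher exact | 93.5% | 88.1% | 82 |
| Continuity-corrected z (power by full enumeration, n by formula) | 93.5% | 88.1% | 90 |

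One-sided, the methods straddle 95%, as expected if the calculation was one-sided. Two-sided, none reaches 95% at 65; the range is 88.1% to 92.8%.

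**Step 4. Power at the completers implied by the recruitment target.** 115 × (1 − 0.20) = 92 per group.

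Two-sided pooled z: 0.20 × √92 = 1.9183; Φ[(1.9183 − 0.9897)/0.4848] = Φ(1.916) = 97.2%. Fisher exact gives 96.9%, and full enumeration of the pooled z test gives 98.2%. The 92 completers exceed every two-sided requirement in the table.

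**The case against.** **A one-sided test is unstated, not contradicted.** The assumption is directional (relapse in AN above expression in HC), and the other 0.05 in the section belongs to the mixed models. The sidedness of the final analysis may be set in an analysis plan that is not shown. This stands as far as it goes: the documents do not show that a one-sided test would be wrong. It does not rescue the power statement, which is presented as a completed calculation and omits the input on which its answer depends.

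**The practical harm is small.** A reader might infer that the study is underpowered, or that its type II error is double what is claimed. The documents do not support that. The doubling applies only if about 65 per group complete. On the protocol's own 20% dropout, 92 complete, and two-sided power exceeds 95% by the pooled z, exact z and Fisher calculations.

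**The contrast is not a stated hypothesis.** Hypothesis 2a concerns prediction of relapse or remission within AN, and none of the listed hypotheses compares relapse in AN with expression in HC. So correcting this power figure says nothing either way about the reliability of the stated aims. It remains the only basis given for the sample size and should be right.

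**The effect-size wording.** The protocol writes "Taking a conservative approach (equivalent to a medium effect size), we estimated a relapse probability of 25% within the AN sample". A reader might infer that the effect is not really medium and the choice not conservative, because 25% against 5% is Cohen's h = 0.60 and an odds ratio of (0.25/0.75)/(0.05/0.95) = 6.3. The documents do not support this. No effect-size index is named. By the usual benchmarks, which are an outside convention, h = 0.60 lies nearer medium (0.5) than large (0.8), and w = 0.20/(2 × √(0.15 × 0.85)) = 0.28 is just below medium (0.3). The assumed 25% also lies below the 30-50% lifetime relapse range cited in the same section, which gives the word conservative a basis for the AN rate.

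**Conclusion.** The point holds for the power statement tied to 65 completers. The pairing of 65 per group with 95% power at alpha 0.05 is reproduced only by one-sided methods, and the protocol declares no one-sided test. Read as two-sided, power at 65 is about 90% (88% to 93% across methods), and 95% needs about 80 per group (74 to 90).

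The conclusion rests on the protocol's own 25% and 5% and on equal groups. The further statement that recruitment is adequate, at about 97% two-sided power, depends on dropout staying near 20%. Two-sided power falls to the 90% figure only if loss reaches 1 − 65/115 = 43%. The defect is therefore an undeclared side in a power statement, not a shortfall in planned recruitment.

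**What to change.** In section E, name the test used for the two proportions and its sidedness. Then do one of the following:

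- restate the power as about 90% at two-sided 0.05 with 65 completers per group, and about 97% with the 92 per group expected from 115 recruits less 20% dropout; or
- keep the 95% and say explicitly that it refers to a one-sided 0.05 test.

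Optionally, name the index behind the medium label (h = 0.60, w = 0.28); the label itself need not change.

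The cost is wording only. No extra participants are needed. The one drawback, under the first option, is a less favourable stated power at 65 completers.

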## **G. Human Participants**

We aim to recruit a total of 230 human subjects:

- 115 females with anorexia nervosa (AN), age 15 – 40 years.
- 115 healthy comparisons (HC), females, ages 15 – 40 years, who will be recruited to match to the AN sample based on age.

AN Inclusion criteria:

- i. Primary clinical diagnosis of anorexia nervosa as defined by Laureate Eating Disorders Program
- ii. Body mass index  $\geq 18.5$ . BMI cannot be below 18.5 within 1 week of capsule swallow.
- iii. Transitioned from acute clinical status rating to residential clinical status or partial/intensive outpatient clinical status rating
- iv. May be on SSRI and SNRI medications, as well as atypical antipsychotics, tricyclic antidepressants, buspirone, and lamotrigine.
- v. No new medication prescription in the week prior to study randomization, Must be on a stable dose of medication for at least 1 week.
- vi. Females, ages 15 to 40 years
- vii. Women of childbearing age: a hormonal (i.e., oral, implantable, or injectable) and single-barrier method, or a double-barrier method of birth control must be used throughout the study.
- viii. Independently ambulatory
- ix. Possession of a smartphone with data plan
- x. English proficiency
- xi. Willingness and ability to participate in study procedures
- xii. Provision of signed and dated informed consent form

AN Exclusion criteria:

- i. Active suicidal ideation with intent or plan
- ii. Active cutting or skin lacerating behaviors
- iii. Active purging behaviors (specifically, self-induced vomiting), and/or a history of severe self-induced vomiting
- iv. Pregnancy as defined by a urine screen during screening, and confirmed during each stimulation visit, and must not be lactating
- v. History of significant gastrointestinal disorder, including any form of inflammatory bowel disease or gastrointestinal malignancy (celiac disease is accepted if the subject has been treated and is in remission)
- vi. History of complicated/obstructive diverticular disease
- vii. Clinical evidence of significant gastroparesis
- viii. Diagnosis of mega-rectum or colon, congenital anorectal malformation, or clinically significant rectocele or rectal prolapse
- ix. History of intestinal or colonic obstruction, or suspected intestinal obstruction

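### Recruiting 115 per group does not follow from 65 completers and 20% dropout: those inputs give 82 recruits, while 115 recruits give 92 completers or imply 43% loss

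*Protocol*

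**What the plan says.** The only sample-size justification in the protocol is in section E (Statistical Methods). It compares two independent proportions over the six months after discharge. For the patients, "we estimated a relapse probability of 25% within the AN sample"; for the healthy comparisons, it assumes "an expression rate of 5% within the HC sample over the course of the study period". With "95% power (1-beta error probability") and "at an alpha error probability of 0.05", the calculation "yielded a total sample size of 130 subjects (n=65 completers per group").

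The same sentence then moves from completers to recruits: "note that we aim to recruit 115 participants per group to account for an estimated 20% dropout rate across all study phases".

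The target is not a local slip. Section G (Human Participants) says "We aim to recruit a total of 230 human subjects", split 115 and 115. The Recruitment paragraph of section D also gives 115 per group, and the later Recruitment paragraph gives 230 in total. No other allowance (screen failure, unusable recordings, separate rates for separate phases) is given to bridge 65 and 115.

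**The concern.** The sentence presents 115 as the number that protects 65 completers against 20% dropout. A 20% allowance raises a sample by a quarter, but going from 65 to 115 raises it by 77% (50/65). At least one of the completer count, the dropout rate and the recruitment target is therefore misstated, or a further allowance has been left out.

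What is at stake depends on which figure is wrong:

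- **If 20% is right,** the plan enrols 66 more people than its own calculation calls for. They include adolescents from age 15, and section H lists bowel obstruction among the possible capsule risks and says participants may have no direct benefit. An ethics committee needs a correct reason for that number.
- **If a loss of about 43% is really allowed for,** the stated 20% understates attrition. The relapse outcome behind the sample size is followed up remotely through self-completed scales (section D, Follow up). Missing-outcome bias is a much larger worry at 43% loss than at 20%.

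In both cases a reader cannot tell whether the study is planned around 65 or 92 completers per group.

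**Working it through.** **Inputs, all from section E of the protocol:** 25% and 5% event rates, alpha 0.05 (sidedness not stated), power 95%, 65 completers per group, one dropout rate of 20% over all phases, 115 recruits per group.

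**Step 1. The completer count.** Pooled normal approximation for two proportions:

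n = [z(alpha) × √(2 × 0.15 × 0.85) + z(power) × √(0.25 × 0.75 + 0.05 × 0.95)]² / (0.25 − 0.05)²

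The two square roots are √0.255 = 0.505 and √0.235 = 0.485.

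| Test | Power | n per group |
|---|---|---|
| One-sided 0.05 | 95% | 67 |
| Two-sided 0.05 | 90% | 65 |
| Two-sided 0.05 | 95% | 80 |
| Two-sided 0.05, continuity correction | 95% | 90 |

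At the stated 95% power, 65 is approximately reproduced only by a one-sided test, where power at 65 is 94.7%. That is a side issue, and the dropout step below takes 65 as given.

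**Step 2. From completers to recruits.** With dropout d, recruits = completers / (1 − d).

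- Correct inflation: 65 / 0.80 = 81.25, so 82 per group and 164 in total.
- Common shortcut: 65 × 1.20 = 78.
- Stated: 115 per group and 230 in total.
- Excess over the stated inputs: 115 − 82 = 33 per group, 66 in total.

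**Step 3. From recruits back to completers.**

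- 115 × 0.80 = 92 per group, 184 in total.
- 92 against 65: 27/65 = 42% more.
- Loss needed to go from 115 to 65: 50/115 = 43.5%.

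**Step 4. Could 20% apply to each phase?**

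| Phases | Recruits needed for 65 completers | Completers left from 115 |
|---|---|---|
| 1 | 82 | 92 |
| 2 | 102 | 73.6 |
| 3 | 127 | 58.9 |

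No whole number of phases links 65 to 115.

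**Step 5. What 115 does fit.** 92 / 0.80 = 115 exactly. The continuity-corrected two-sided figure from step 1 gives 90 / 0.80 = 112.5, so 113, which is close. Both suggest a completer count near 90 behind the target, but the protocol does not document one.

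**Step 6. Effect on power (25% against 5%, alpha 0.05).**

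| Completers per group | One-sided | Two-sided | Two-sided Fisher exact |
|---|---|---|---|
| 65 | 94.7% | 90.1% | 88.1% |
| 92 | 98.8% | 97.2% | 96.9% |

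**The case against.** The strongest reply is that the figures can coexist. A study may need 65 completers, expect 20% loss and still recruit 115, because 92 expected completers exceed 65. The later Recruitment paragraph words the total of 230 as an upper limit. On this view the flaw is an unexplained margin in the safe direction, and power is not threatened. The larger sample also has an evident use: the within-patient prediction hypotheses in Aim 2 depend on the number of relapses, and at 25% there would be 23 among 92 completers (92 × 0.25) against about 16 among 65.

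A second reply is that people are consented before eligibility is settled (section D, Screening assessment), so losses beyond dropout are foreseeable.

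Part of this stands. The study is not made underpowered against its own calculation, the extra participants may well be useful, and no sentence in the protocol actually expects 43% loss; that figure is only what 115 and 65 imply together.

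The rest does not hold against the text. Section E gives dropout as the sole reason for 115 and mentions no margin or secondary aim. Section D plans to obtain measurements from 115 per group, so screen failures after consent do not bridge the gap. The dropout rate is worded as one overall figure, and reading it per phase misses 115 anyway.

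**Conclusion.** The concern holds. Taking 65 completers and 20% dropout as printed, the target should read 82 per group, not 115: a gap of 33 per group and 66 in total. Taking 115 and 20% as printed, the study should expect 92 completers, not 65. Taking 115 and 65 as printed, the assumed loss is 43.5%, more than twice the stated rate. These results use only the protocol's own numbers and the usual inflation by 1/(1 − d). They do not depend on the sidedness of the test or on whether 65 itself is right.

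The protocol does not show which of the three figures is wrong. That 115 is exactly 92/0.80 points to the completer count, but this is inference. The consequence is limited, because the mismatch runs towards more participants rather than fewer. It still needs correcting, because it is the only justification given for the size of the enrolment.

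**What to change.** Replace the sentence in section E with one consistent chain. Either:

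1. State 115 recruited per group, 20% overall dropout and 92 completers per group, and recompute the one stated power figure at 92 (97.2% two-sided or 98.8% one-sided for 25% against 5%), naming the sidedness; or
2. Keep 65 completers, and state the attrition of about 43% that 115 allows for, broken down by phase, with the reason for expecting it.

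If the extra recruits are meant as a margin for the EEG, computational or prediction aims, or for unusable data, say so and give the amount. The second option should also confirm how 65 was obtained, since at 95% power it is approximately reproduced only by a one-sided test.

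The cost is one sentence in the protocol. The targets of 115 and 230 elsewhere can stay, and no procedure or analysis changes.
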